### Randomization and blinding

A total of 68 eligible FAI participants will be randomized 1:1 to an intervention group or a control group by simple randomization. Random sequences will be computer-generated through the SAS Statistics software version 9.4 (SAS Institute Inc. Cary, NC) by an independent researcher, who will not be involved in baseline data collection, clinical interventions, functional outcome assessments, data collection, or statistical analysis. The allocation of participants will be concealed through enclosing assignments in sequentially numbered, opaque-sealed envelopes. Clinicians will determine whether subjects can participate in the study in strict accordance with the above inclusion and exclusion criteria. All subjects who agreed to participate and determined that they were suitable to participate in the study will be randomized. The researchers responsible for recruitment will assign the eligible number and in turn receive a closed opaque envelope with randomization numbers, allocation, and intervention information inside. Then they give the envelope to the clinician or therapist. It should be noted that the researchers responsible for recruiting subjects will not be allowed to know about the group assignments. The clinical intervener will open the envelope and learn about the intervention plan to be administered to the participants. Due to the nature of the clinical intervention, the participants, clinician, and therapist cannot be blinded after assignment to intervention. The outcome assessors and data statisticians will not know the treatment allocation until all data analyses have been completed.

### Interventions

#### Control group

Subjects in the control group will receive CBT based on the Single-Legged Balance Training Program. The program consisted of a warm-up exercise, the single-legged stance, single-legged stance with bosu ball exercises, single-legged stance with kicking against resistance in four directions, and step-down with single-legged in four directions. The training difficulty of this exercise prescription is from easy to difficult. In the training process of this experimental study, the subjects were required to keep the body center of gravity stable during the training process, 40 min each time, 3 times a week for 12 weeks.

In addition to the CBT, all participants will receive health education at the start of the study and monthly throughout the study period. FAI is mainly characterized by recurrent “muscle weakness” of the ankle joint associated with ankle pain, muscle strength weakening, proprioception decline, and random control disorders of joint movement. Therefore, it is necessary to inform them of the preventive measures for ankle sprain, instruct them to properly rest, correct their bad exercise patterns (avoid acute jumping, climbing mountains, and other activities that damage joints), and wear ankle protection when necessary. In addition, patients with ankle joint injury are often anxious and corresponding psychological nursing can be carried out to relieve the anxiety and worry of patients.

### Experimental group

On the basis of health education treatment in the control group, the TCC intervention group will undergo a 40-min 24 Simplified Yang-style TCC exercise. Yang-style TCC consists of slow, smooth, and rhythmic movements that emphasize the practitioner's focus on trunk rotation, weight shifting, coordination, and maintenance of lower limb posture stability. Subjects with FAI will be taught and supervised by an expert TCC coach to ensure the unity of practice time and the basic correctness of action rhythm. The complete set of TCC exercises consists of three parts: 5-min warmup, 30-min TCC practice, and 5-min cool down. Practice will occur once per day, three times a week for 12 weeks, for a total of 36 times.

During the whole training process, patients are encouraged to keep practicing if they have slight ankle pain. If the ankle joint pain of the subject is obvious during the training, i.e., VAS > 3 points, we will suggest the subject to rest or suspend the training, and continue after the pain is relieved.

### Demographic parameters

Before all subjects are enrolled, we will collect their demographic characteristics, including age (year), gender (male, female), height (cm), weight (kg), body mass index (kg/m^2^), marital status (single, married, divorced), occupational status (full-time worker, part-time worker, unemployed), affected ankle (left, right), Baseline Cumberland Ankle Instability Tool score, no. of sprains, initial ankle sprain evaluated by a medical professional (yes, no), time since first sprain (year), and time since last sprain (month).

### Outcome measurements

Outcome measures will include postural stability and self-reported instability feelings that will be performed at baseline, post-intervention, and 3-month follow-up.

## Patient-reported outcomes

### Cumberland ankle instability tool

The Cumberland Ankle Instability Tool (CAIT) (22) is used to focus on the severity of functional problems in patients with ankle instability, which is recommended by the International Ankle Consortium. It consists of nine items and is scored on a 30-point scale. Previous research shows that the Chinese version of CAIT is a valid and reliable questionnaire tool to evaluate ankle function in clinical trials. CAIT scale can distinguish between patients with and without CAI. A higher response score represents a better level of overall function and ankle stability, and values ≤ 25 represent ankle instability. According to a recent study, the minimum detectable change score of CAIT is ≥3, which can be used to determine the effectiveness of CAI interventions. Thus, in this study comparisons of CAIT scores before and after treatment are used as the primary outcome measure of functional improvement in patients with FAI.

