As far as we know, only one research group has reported that TCC intervention has a positive effect on postural control and self-reported instability feeling in patients with CAI but failed to compare the clinical effects with other training programs (18). Moreover, there is no literature directly examining the comparative effects of TCC intervention and conventional balance training (CBT) protocols regarding their impact on postural stability and self-reported outcomes in patients with FAI. From the perspective of clinical utility, it is extremely interesting to see which intervention is more effective as clinicians always want to be able to select the best intervention for patients with FAI. Theoretically, patients with FAI are a series of complex clinical syndromes resulting from the interaction of pathomechanical, sensory perceptual, and motor behavior impairments (19, 20). Balance training alone may only achieve partial therapeutic effects. TCC is a kind of mind–body exercise that may be particularly beneficial to FAI because it involves movement recall, task switching, attention, and visuospatial processing simultaneous with physical movements (21). Therefore, our hypothesis is that both TCC intervention and CBT would obtain significant improvements, with a possible superiority of TCC over CBT. Thus, the aim of this randomized controlled study is to test the comparative effects of TCC intervention and CBT protocols in improving postural balance and subjective instability feelings in patients with FAI.

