## Methods and analysis

### Study design and setting

This study will be a single-center, randomized, exploratory trial with two parallel groups. The objective is to test the comparative effects of TCC intervention and CBT protocols in improving postural balance and subjective instability feelings in patients with FAI.

We recruited subjects from the Fujian Provincial Hospital, the surrounding Sports Center, and residents of Gulou District, Fuzhou City, Fujian Province, China. Potential eligible subjects who meet the following inclusion criteria but are excluded from the exclusion criteria will be determined by two orthopedic surgeons for eventual inclusion in the study. After signing the written informed consent form, eligible participants will be randomly divided into two groups, the intervention group or the control group, at a 1:1 ratio. All assessments will be conducted at baseline, post intervention, and 3-month follow-up. This study was designed in strict accordance with the Standardized Protocol Items, including the Recommendations for Interventional Trials (SPIRIT) Checklist, and has been approved by the Ethical Committee of Fujian Provincial Hospital (no. k2019-03-035). In addition, we have completed registration in the Chinese Clinical Trials Registry in 2021. The flow diagram for this trial is shown in Figure 1. The specific flowchart of participant recruitment is shown in Table 1.

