### Sample size

Sample size calculations were done using the G-power 3.1.9.2 software (developed by the University of Düsseldorf, Germany). An effect size of 0.8 and a two-sided alpha level of 0.05 were set based on the differences of pre- and post-treatment repeated measurement points of Star Excursion Balance Test (SEBT) and CAIT; a total sample of 56 participants (28 patients in each group) is required to achieve 90% power. The estimated withdrawal rate was 10–20%, and a total of 68 participants (34 patients in each group) were planned to be enrolled in this clinical trial. The power analysis is based on the primary outcome variable, including within-group differences in SEBT and CAIT (dependent variables) before and after treatment. The means and standard deviations of the SEBT and CAIT are based on the results from a similar published study from Spain (18) and preliminary experiment of the research group (intervention group: ▴SEBT-posteromedial M = 6.46, SD = 6.89, ▴CAIT M = 10.8, SD = 2.21, control group: ▴SEBT-posteromedial M =0.64, SD = 3.86, ▴CAIT M =0.2, SD = 2.10), with a 1:1 allocation ratio.

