### Data analysis

Statistical analysis will be carried out using SPSS Statistics, version 22.0 (SPSS Inc., Chicago, IL, USA). All assigned subjects with available data will be analyzed according to the intention-to-treat principle. Continuous variables, such as CAIT score, age, and disease duration, will be expressed as mean ± standard deviation (SD) or medians (25th to 75th centiles), depending on whether the distribution of variables is normal or skewed. For other categorical data, we will use Mann–Whitney test, chi-square test, or Fisher's exact test for statistical analysis as appropriate. Multiple-measure variables will be analyzed by repeated-measures ANOVA. Additionally, we will use the last-observation-carried-forward method to deal with the missing data. Statistical significance will be assessed as *p* < 0.05.

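### The primary outcome and power basis are worded as before-versus-after comparisons, which do not test TCC against CBT, and the planned ANOVA names no deciding term or time point

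*Protocol article*

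**What the plan says.** The protocol article states the question one way and the primary comparison another.

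- **Objective** (Study design and setting): "The objective is to test the comparative effects of TCC intervention and CBT protocols in improving postural balance and subjective instability feelings". This is a between-arm question.
- **Hypothesis** (Background): "both TCC intervention and CBT would obtain significant improvements, with a possible superiority of TCC over CBT". It has a within-arm part and a between-arm part.
- **Primary outcome** (Cumberland ankle instability tool): "comparisons of CAIT scores before and after treatment are used as the primary outcome measure of functional improvement in patients with FAI". No arm contrast and no visit is named.
- **Power basis** (Sample size): "The power analysis is based on the primary outcome variable, including within-group differences in SEBT and CAIT (dependent variables) before and after treatment".
- **Analysis** (Data analysis): "Multiple-measure variables will be analyzed by repeated-measures ANOVA". No factor, term, time point or role for baseline is given.
- **Visits** (Outcome measurements): outcomes are "performed at baseline, post-intervention, and 3-month follow-up". Table 1 places the post-intervention assessment at week 13. The Demographic parameters section lists baseline CAIT among the data collected.

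**The concern.** Both arms receive an active programme, so an improvement over time within an arm does not show that TCC is better than CBT. The two places that describe the primary comparison nevertheless describe that improvement. An analysis plan written to this wording could report two significant before-after changes, or one significant and one not, without ever estimating the difference the trial was set up to measure.

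The ANOVA sentence does not settle the matter. A repeated-measures ANOVA yields a time effect, a group effect and a group-by-time interaction. The time effect does not compare the arms. The other two do, but they have different power and neither isolates a visit. If the deciding term is not named in advance, it can be chosen after the results are seen.

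**Working it through.** **1. The plan's own sample size.** Inputs (Sample size): effect size 0.8, two-sided alpha 0.05, power 90%, 28 per group.

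- Two-sample t-test, two-sided: 34 per arm needed; 28 per arm gives 83.6%.
- Two-sample t-test, one-sided 0.05: 28 per arm gives 90.5%.
- Paired (within-group) t-test, two-sided: 19 per group; one-sided: 15.

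Of these, only the one-sided two-sample test returns 28 per arm. The arithmetic is therefore between-arm in form although the text calls it within-group. The mismatch with the stated two-sided alpha is a separate matter.

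**2. What each candidate test delivers.** Setting: n = 28 per arm, SD 1 at every visit, equal correlation r between visits (assumed; the article gives none), true arm difference 0 at baseline and 0.8 at week 13. At 3 months it is either 0.8 (sustained) or 0.4 (halved). The ANOVA is assumed to take the three visits as levels.

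- *Group-by-time*, 2 and 108 df: noncentrality = (n/2) × SS/(1 − r), where SS is the sum of squared deviations of the three visit differences from their mean. SS = 0.427 sustained and 0.32 halved. At r = 0.5 sustained: 14 × 0.427/0.5 = 11.95.
- *Group main effect*: difference in three-visit means, (0 + 0.8 + 0.8)/3 = 0.533 or (0 + 0.8 + 0.4)/3 = 0.40, over SD √[(1 + 2r)/3]. At r = 0.5 sustained: 0.533/0.816 = 0.65.
- *Week-13 ANCOVA*: standardised difference 0.8/√(1 − r²). At r = 0.5: 0.924.

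| Power, 28 per arm | r = 0.3 | r = 0.5 | r = 0.7 |
|---|---|---|---|
| Group-by-time, sustained | 73% | 87% | 98% |
| Group-by-time, halved | 60% | 76% | 94% |
| Group main effect, sustained | 77% | 67% | 59% |
| Group main effect, halved | 52% | 44% | 38% |
| Week-13 ANCOVA (either case) | 87% | 92% | 98% |

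Simulation agrees to within about one percentage point: group-by-time halved 61%, 75% and 93%; ANCOVA 86%, 92% and 98%. The formula for ANCOVA ignores chance baseline imbalance, so the simulated figures are used below.

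**3. Separate within-arm tests.** Suppose both arms truly improve by the same 0.5 SD of change. The two-sided paired t-test with 28 patients has power p = 0.723. Exactly one arm is significant with probability 2p(1 − p) = 2 × 0.723 × 0.277 = 0.40. With a common improvement of 0.4, 0.6 or 0.8 SD the probability is 0.50, 0.23 or 0.03.

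**4. Sample size under an adjusted week-13 contrast.** The unadjusted n per arm is 2 × (1.960 + 1.282)²/0.8² = 32.8. Multiplying by (1 − r²) gives 30, 25 and 17 per arm for r = 0.3, 0.5 and 0.7. If 0.8 is instead in SD units of the change score, the multiplier is (1 + r)/2, giving 22, 25 and 28. With 34 enrolled per arm and the stated 10–20% withdrawal, 34 × 0.9 = 30.6 to 34 × 0.8 = 27.2 per arm remain.

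**The case against.** The strongest reply is that the CAIT sentence defines a variable (change in CAIT), and that the objective supplies the contrast. The Sample size section quotes change scores for both arms with 1:1 allocation, and 56 fits only a two-sample formula. This shows that a between-arm comparison was probably intended. It does not remove the contradiction: the power sentence says within-group in terms, and no section names an arm difference as primary.

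It is also fair to say that an article may leave model terms and covariates to a fuller document. The list of abbreviations includes generalized estimation equations, which the text never uses, so fuller analysis text may exist. The missing covariate alone would therefore be no finding. The point rests on what the article does state about the primary comparison.

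Group-by-time is a legitimate between-arm test, and at r = 0.7 with a sustained effect it matches ANCOVA. That stands, so the loss of power ranges from none to material. Its remaining weakness is that it does not say at which visit the arms differ.

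A reader might infer more than the article supports:

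- *That baseline is fixed as an outcome level.* This is the usual reading of three visits in a repeated-measures ANOVA, but it is not stated.
- *That the group main effect is the planned test.* No term is named, so its low power is a risk and not a property of the plan.
- *That entry on CAIT ≤ 25 biases the comparison through regression to the mean.* It can inflate before-after change in each arm. In expectation it acts equally on two randomised arms and does not bias TCC against CBT.
- *That superiority will be claimed from one significant and one non-significant arm.* Nothing in the article plans this; the 40% figure shows why it must be ruled out.

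**Conclusion.** The point holds as a mismatch between the question and the stated primary comparison, together with an unnamed deciding test. It does not show that the trial cannot compare TCC with CBT, because the design and data allow it. It should be fixed; the trial calls itself exploratory, and the remedy is wording.

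At 28 per arm and a true 0.8 SD difference at week 13, leaving the decision to group-by-time costs about 13, 5 and 0 percentage points of power against baseline-adjusted week-13 analysis at r = 0.3, 0.5 and 0.7. If the effect halves by 3 months, the cost is about 25, 17 and 5 points. Deciding on the group main effect would cost about 25 points at r = 0.5 with a sustained effect. At r = 0.3 with a sustained effect it would do slightly better than group-by-time (77% against 73%), though still below ANCOVA. These figures rest on the assumed correlation, compound symmetry and the two assumed effect patterns. The contradiction in wording rests on none of them.

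**What to change.** **Cumberland ankle instability tool and Data analysis.** State that the primary analysis is the TCC minus CBT difference in CAIT at week 13, with its 95% confidence interval, adjusted for baseline CAIT. ANCOVA would serve, as would a mixed model or a constrained longitudinal model with a named week-13 contrast. The choice among them matters less than naming the contrast. Make the 3-month contrast secondary. Report within-group changes descriptively, and say that they will not be used to infer efficacy or superiority.

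**Sample size.** Reword the power basis as a between-group difference, and say whether 0.8 is in SD units of the week-13 score or of the change score.

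**Cost.** Analysis wording only; baseline CAIT is already collected. For an effect of 0.8 the planned 68 need not grow, provided about 28 to 30 per arm remain. At r = 0.3 with 28 per arm, power is about 86% and not 90%, which is still above the alternatives in the table. The sponsor gives up within-group significance as evidence of efficacy. As recruitment was due to start in November 2022, the change should be dated and made before allocation is revealed to the statisticians.

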### American orthopedics foot and ankle society's ankle–hindfoot evaluation scale

American orthopedics foot and ankle society's ankle–hindfoot evaluation scale (AOFAS-AHES) (23) is specifically used to estimate clinical problems of the ankle–hindfoot. The cultural adaptation and validation of the Chinese version of AOFAS-AHES has also been successfully implemented. It includes subjective or patient-reported items, as well as objective or physician-assessed items, on a scale of 0–100, with higher scores indicating better function. According to the scoring results, it can be divided into four grades: excellent (90–100 points); good (75–89 points); acceptable (50–74 points); and poor (< 50 points).

### The MOS item short form health survey

Short form health survey (SF-36) (24) is a concise health questionnaire developed by the Boston Institute of Health in the United States, and the Chinese version of SF-36 has been widely used in clinics. It is widely used to measure the quality of life of the general population as well as in the evaluation of the effect of clinical trials and the evaluation of health policies. The SF-36 is a concise health questionnaire that comprehensively summarizes the respondents' quality of life from eight dimensions: physiological function, physical pain, general health status, energy, social function, emotional function, and mental health. It has been reported that SF-36 is a general health assessment tool that can assess the impact of ankle-related diseases on their quality of life.

### Static balance

In this study, TecnoBody ProKin (ProKin Software Stability, TecnoBody S.r.l., Dalmine, 24044 Bergamo, Italy) will be used to evaluate the static postural control ability of the affected side's foot in patients with FAI. Subjects will be asked to stand on a balanced platform and pressure sways in all directions will be detected. First, subjects will be instructed to look directly at a front screen surface, and then they will be asked to try to maintain their balance on both the legs for 60 s, initially with their eyes open and then closed. Subsequently, patients will be asked to try to maintain their balance for 60 s on the affected side leg for 60 s with their eyes open and then closed. We will obtain the change of center of pressure (COP) of the lower limbs from the subjects. Among these, the static balance ability indexes include the length (mm) and average speed (mm/s) of body sway [total and along the anteroposterior (AP) and mediolateral (ML) axis] and area of body sway (area of the ellipse; mm^2^).

The total length of body swing (perimeter; mm) was calculated as the total length of the distance the center of gravity movement route recorded by the system during the subject's body swing, reflecting the total distance and shaking degree of the center of gravity of the human body. The greater the value, the worse the stability. Area of body sway (area of the ellipse; mm^2^) refers to the area of the center of gravity movement of the human body. The larger the area, the worse the stability.

### Dynamic balance

This study will use a posturographic balance platform to perform dynamic balance tests to evaluate proprioception. The ProKin used in this study is an advanced technology that combines classic tilting platform connected to monitors and speakers. By creating visual and audio feedback, it can respond to the minimum movement of the platform on all planes (25). The movable balance platform in this system can detect balance measurement in all directions with an operating angle of 15°C. The index of dynamic balance ability is the total offset index, which refers to the angle between the position of the patient's overall offset and the vertical midline. The average trace error (ATE) was calculated for the proprioception index. ATE = (track length traced by the patient's ankle foot control cursor – ideal track length)/ideal track length. The greater its value, the worse the posture control ability. Also, 0–35% of ATE is considered very good, 35–100% is considered sufficient, and >100% is considered to indicate problems in proprioceptive control (26).

